### Implementation Protocol

During routine consultations, primary health care providers will assist caregivers in registering for the iCURE WeChat service account. Upon registration, all caregivers will complete a questionnaire providing demographic information, their child’s injury history, and an injury risk assessment survey.

Caregivers randomly assigned to the intervention group will then receive the full version of the iCURE program, including real-time feedback, tailored educational content, and access to the Q&A module. The control group will access a simplified version involving completion of assessment surveys that are used only for data collection; they will receive no feedback, education, or supplemental materials. Both groups will continue to receive routine safety education provided by preschool teachers and primary health providers. Group allocation is detailed in Table 1. Details regarding the timeline for recruitment and intervention period are shown in Figure 3.

**Table 1. T1:** Functions of iCURE (Intelligent Child Unintentional-Injury Reduction & Education) used by intervention group and control group.

Functions	Intervention group	Control group
Data collection	✓	✓
Injury risk assessment	✓	✓^a^
Instant feedback	✓	
Tailored education	✓	
Interactive questions and answers	✓	

a Control group will complete the injury risk assessment for data collection purposes, with no risk evaluation reports provided.

**Figure 3. F3:**
[figure not shown]
Timeline for the schedule of enrollment, interventions, and assessments. iCURE: Intelligent Child Unintentional-Injury Reduction & Education.

### Outcomes

The primary outcome is unintentional injury incidence, calculated as:

$$\frac{Number\;of\;children\;with\;injuries\;during\;the\;12-month\;study\;period}{Total\;number\;of\;children}\times 100\%$$

Injury events will be identified based on established criteria from previous studies [48], defined as any of the following: (1) receiving medical attention at a health care facility and being diagnosed with a specific injury; (2) receiving first aid from a nonmedical responder (eg, family member and teacher), such as wound dressing or bandaging; and (3) missing school for more than half a day due to an injury. We will also compare injury rates at 3-month intervals to assess the effect over time.

In addition, several secondary outcomes will be assessed:

(1) Change in child injury risk level: A 46-item questionnaire will assess children’s risk of unintentional injury, classifying children as low-to-moderate or high risk. The questionnaire was adapted from existing validated instruments and covers 8 common types of injuries: drowning (5 items), road traffic injuries (6 items), choking (6 items), falls (6 items), burns and scalds (6 items), poisoning (5 items), animal bites (5 items), and sharp and blunt object or foreign body injuries (7 items) [43-47].

(2) Change in caregiver supervision behavior score: Caregivers’ caregiver supervision behavior will be measured using a simplified version of a validated 5-item questionnaire, with responses rated on a 5-point Likert scale [49]. Items overlapping with the child injury risk assessment questionnaire were excluded to avoid redundancy.

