Injury risk assessment: a comprehensive child injury risk assessment questionnaire, developed based on validated tools [43-47], to assess child age, caregiver and child behaviors, and environmental risk.Instant feedback: upon completing the risk assessment, participants receive immediate feedback and tailored recommendations generated by an integrated expert classification system and a decision tree model. This system stratifies children into low or moderate risk or high risk, which supports further personalized prevention strategies. For research purposes, participants who are randomly assigned to the control group will complete the assessment but will not receive feedback. Caregivers of children in the intervention group who are identified by the system as “high risk” will receive item-specific risk reports. This individualized risk profile will guide the dissemination of AI-tailored education materials for each child.Injury reporting: caregivers are encouraged to report any injury events their children experienced during the study period. The module facilitates timely documentation and monitoring of injury events.Interactive questions and answers (Q&A): caregivers may submit injury prevention questions through the platform’s real-time Q&A interface, which provides instant computer-generated and automated responses. The iCURE platform uses a hybrid natural language processing approach that combines keyword matching and text similarity analysis to retrieve and deliver relevant, automated responses from a curated injury prevention knowledge base created by the research group.Tailored education: personalized educational content on child injury prevention is delivered in various formats (eg, text, images, long-form infographic post, flyers, and short videos). Delivery frequency is determined by a rule-based decision logic algorithm and tailored to the child’s risk level; caregivers of low-risk children receive content once per week, while those with higher-risk children receive it 2 or 3 times per week.

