### Data Analysis

Data will be analyzed following intention-to-treat principles and including all participants as originally assigned, regardless of adherence. Descriptive analysis (mean, SD, median, IQR, and proportion) will be used to describe baseline characteristics by groups. Differences in unintentional injury incidence across 5 timepoints (baseline, 3, 6, 9, and 12 mo) and other outcomes at 2 timepoints (baseline and 12 mo) will be examined using rank-sum tests for ordinal outcomes, chi-square tests for categorical outcomes, and independent 2-sample *t* tests for continuous outcomes. Within-group changes over time will also be evaluated.

Generalized linear mixed models with a Poisson link function will be used to compare the 12-month injury incidence between groups, adjusting for baseline covariates and accounting for clustering at the street or town level. Risk ratios and 95% CIs will be reported. Generalized estimating equations will also be used to assess repeated measures of injury incidence across follow-up timepoints, providing population-averaged estimates while accounting for within-subject and within-cluster correlations. Secondary outcomes, including changes in injury risk levels and caregiver supervision behaviors, will be analyzed using regression models appropriate to the type and distribution of the variable. User engagement indicators will be included as covariates of the effectiveness analysis model.

Two sets of sensitivity analyses will be performed to assess the robustness of findings: (1) per-protocol analyses and (2) models excluding participants with missing primary outcome data. Missing data will be documented and addressed using appropriate statistical methods as needed.

This study will adhere to the CONSORT (Consolidated Standards of Reporting Trials) 2025 [52] statement to perform data analysis and report results.

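### The first secondary outcome is change in a two-level class built from 46 items, so change within a class is not counted, and the same instrument drives the intervention's feedback

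*Protocol article*

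**What the plan says.** All references are to the Protocol article.

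- **Outcomes.** The first secondary outcome is named "Change in child injury risk level" and is described thus: "A 46-item questionnaire will assess children’s risk of unintentional injury, classifying children as low-to-moderate or high risk". The next secondary outcome is named "Change in caregiver supervision behavior score". The article therefore uses a score for one outcome and a level for the other.
- **Data Analysis.** The level is named again: "Secondary outcomes, including changes in injury risk levels and caregiver supervision behaviors, will be analyzed using regression models", with the model to suit the type of variable. Outcomes other than injury incidence are compared at baseline and 12 months.
- **Key Components and Content of the iCURE Program.** The same assessment and the same two strata steer the intervention: "This system stratifies children into low or moderate risk or high risk, which supports further personalized prevention strategies". Then: "Caregivers of children in the intervention group who are identified by the system as “high risk” will receive item-specific risk reports". Intervention families in general get feedback and recommendations after the assessment, and low-risk families get educational content weekly.
- **Implementation Protocol and Table 1.** Controls complete the same assessment but receive no report. Both arms continue with routine safety education.
- **Data Collection.** All data are self-reported through the iCURE system.

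**The concern.** Two features of this outcome limit what it can show.

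First, a two-level class records only crossings. A caregiver who removes several hazards counts as unchanged if the child stays in the same class. For a child who starts low-to-moderate, benefit can appear only as worsening avoided.

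Second, the measuring instrument is part of the treatment. Improvement in class is possible only in the high-risk stratum. There, intervention caregivers have been told which items were flagged, and controls have not. When both re-answer the questionnaire at 12 months, a difference may mix real hazard reduction with knowledge of the flagged answers.

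At stake is the reading of one of two listed secondary outcomes. A null result would be less informative than the collected data allow. A positive result could not be read directly as fewer hazards across all enrolled children.

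**Working it through.** **1. Item count.** The eight injury types listed under Outcomes have 5, 6, 6, 6, 6, 5, 5 and 7 items. 5+6+6+6+6+5+5+7 = 46, which agrees with the stated number.

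**2. Possible movements.** With two classes, this holds in both arms by definition:

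| Baseline class | Can improve | Can worsen | Item-specific report |
|---|---|---|---|
| Low-to-moderate, control | no | yes | no |
| Low-to-moderate, intervention | no | yes | none stated (general feedback and weekly content) |
| High, control | yes | no | no |
| High, intervention | yes | no | yes |

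The two high-risk rows are the only ones where improvement can register. They differ in whether the caregiver was shown the flagged items.

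**3. Information kept by a two-level cut (illustration).** Assume a normal underlying score, a small shift in mean, and a share q of children above the cut. The efficiency of the class relative to the score is φ(z)² / [q(1−q)], where z is the normal quantile at 1−q.

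- q = 0.5: 0.3989² / 0.25 = 0.64
- q = 0.3: 0.3477² / 0.21 = 0.58
- q = 0.2: 0.2800² / 0.16 = 0.49
- q = 0.1: 0.1755² / 0.09 = 0.34

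The loss is thus 36% at an even split and 66% at q = 0.1. It exceeds one half only when about 20% or fewer (or 80% or more) are high risk. Under cluster randomisation the loss in total precision is somewhat smaller; it was not quantified.

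**4. Can controls improve? (illustration)** Baseline and 12-month scores were simulated as bivariate normal with assumed correlation 0.7 or 0.9 and assumed q from 10% to 50%. The share of baseline high-risk children who moved to low-to-moderate was:

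- controls, no effect of any kind: 14% to 53%
- intervention, benefit of 0.2 SD: 24% to 63%
- intervention, benefit of 0.5 SD: 41% to 77%

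Across all children, about 6% to 29% changed class in either arm. High-risk controls can therefore move down through ordinary variation alone, so improvement is not confined to the intervention arm.

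**The case against.** The strongest reply has five parts.

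- **Controls can improve too.** A reader might infer that only coached intervention children can improve. The article does not support this: controls are classified on the same instrument and can move down, as step 4 illustrates. What differs between arms is the item-specific report.
- **Worsening counts.** Comparing classes between arms at 12 months also captures low-to-moderate children who are kept from becoming high risk. This stands. The limitation is that no gain within a class registers.
- **Most change being invisible is not shown.** A reader might infer it, but the high-risk share is not given. The class is produced by an expert classification system and a decision tree, not by a stated cut on a normal score. The percentages are generic.
- **Ageing across the boundary is conjecture.** The assessment is said "to assess child age, caregiver and child behaviors, and environmental risk", and the arms differ in age. From Table 2, under 3 years: (579+739)/3110 = 42.4% intervention against (468+619)/3591 = 30.3% control. A reader might infer that ageing 12 months alone could change a child's class. But the eight injury types already account for all 46 items, none of them an age item, and no scoring rule is shown. The imbalance justifies age as a covariate and nothing more.
- **An item count does not cure coaching.** This stands, and the count may be more exposed, because each re-answered item registers without any boundary to cross. It therefore belongs beside the class and should not replace it.

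An analysis plan that is not shown may retain a score. The article itself names only the level, in two places.

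**Conclusion.** The concern holds in a limited form. Three things follow from the article's own definitions without any assumption: change within a class is uncounted; low-to-moderate children can only stay or worsen; and only high-risk children, in either arm, can improve, with item-specific reports going to the intervention arm alone. That re-classification partly reflects knowledge of the flagged answers is a plausible bias whose size cannot be estimated from the article.

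The loss of information, 36% to 66% for high-risk shares from 50% down to 10%, rests on an assumed normal score with a single cut. It shows the order of magnitude and is not an estimate for this trial. The point merits a change because the remedy needs no new data, but it concerns one secondary outcome only.

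**What to change.** Add, as a secondary analysis in all children, the number of items flagged as a risk (0 to 46) at 12 months. Compare it between arms with the baseline count and child age as covariates and with clustering by street or town accounted for. State the rule that makes an item flagged before the 12-month data are analysed; the item-specific reports imply that item-level flags already exist. Keep the two-level class alongside. Report the count also by baseline class, because item-specific reports are described only for high-risk intervention families. Describe both results as self-reported process measures.

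The cost is small. The questionnaire is already completed at baseline and 12 months, so the change is to the wording of the analysis plus the flagging rule. The downsides are that a count weights all items equally, unlike the expert classification, and is less easily explained than a class.

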### Randomization and Blinding

Randomization will be conducted at the street or town level to minimize potential contamination. Each street or town will be randomly assigned to either the intervention or control group, stratified by administrative division, using a random number sequence generated by R 4.4.1 software (R Core Team). The group allocation will remain concealed from both participants and the researcher conducting data analysis.

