## Methods

### Study Design

A double-blind, 12-month, parallel-group cluster randomized controlled trial with 1:1 allocation ratio will be implemented in Changsha, Hunan Province, China. This study will strictly adhere to the SPIRIT (Standard Protocol Items: Recommendations for Interventional Trials) guidelines (Checklist 1)[31,32]. This protocol version is 1.0 and was enacted on August 1, 2024.

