### Strategies to Enhance Engagement

To maximize caregiver engagement with iCURE, we will implement 4 strategies: (1) during registration, caregivers will be instructed to disable the “Do Not Disturb” mode in their WeChat service account; (2) caregivers in the intervention group will earn lottery entries for completing questionnaires and digital points for viewing educational materials, with both entries and points available to be redeemed in ranking competitions, as supported by prior research [28,50] and findings from a needs assessment; (3) safety-themed activities will be organized on designated special days, such as World Drowning Prevention Day, to reinforce injury prevention knowledge; and (4) iCURE materials will be shared through existing WeChat groups by teachers and health care providers in intervention areas to leverage community networks and expand outreach.

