### Data Collection

Primary outcome data will be collected every 3 months to minimize recall bias. Secondary outcomes, which are less sensitive to recall bias, will be assessed annually. The baseline survey includes demographic information, child injury history over the past 12 months, caregiver supervision behaviors, and injury risk assessment, selected based on established associations with child injury and potential confounders [51]. All data will be self-reported, collected via the internet-based iCURE system, and securely stored on encrypted databases and hard drives. Caregivers will receive automated reminders followed by telephone follow-up if necessary to improve response rates.

The iCURE system will automatically record user engagement indicators, including (1) whether educational content was viewed, (2) frequency and duration of viewing, (3) messages to iCURE research team, and (4) online subscription to the iCURE WeChat service account.

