## Discussion

### Anticipated Findings

This protocol outlines a 12-month cluster randomized controlled trial designed to evaluate the effectiveness of iCURE, an intelligent, WeChat-based mHealth intervention for child unintentional injury prevention. The intervention is structured to align with the current primary health care service model in China. If proven effective, iCURE can be generalized and implemented nationwide as a low-cost and easy-to-use unintentional injury prevention intervention.

Childhood injuries result in high morbidity and mortality rates worldwide, including in China. Although injury prevention has been integrated into China’s National Basic Public Health Service system, implementation has been limited due to workforce shortages, high workloads, inadequate training, and the absence of operational guidelines. This study addresses these gaps through the development and evaluation of iCURE. Similar mHealth initiatives have demonstrated effectiveness in child unintentional injury prevention [18-30]. However, unlike traditional app-based programs, iCURE operates via a widely used platform (WeChat) without requiring app installation and incorporates real-time, caregiver-reported injury monitoring. These features are particularly suited to resource-constrained settings and may support scalable implementation in LMICs.

The iCURE program adopts a structured and theory-informed design that is rooted in behavioral science and an injury prevention framework. By integrating an AI-assisted dissemination strategy that is guided by personalized risk assessment reports, it sends individualized and tailored education materials to each caregiver. Leveraging mHealth technologies, iCURE offers cost-effective, easily implementable, and real-time interactive solutions. In addition, the evaluation uses a rigorous cluster-randomized controlled trial design, with blinded outcome assessment and control for potential confounders. It includes clearly defined outcome measures and a standardized data collection process, enhancing the validity of findings.

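### Outcome assessment is not blinded as the article claims: caregivers who visibly receive the intervention self-report every outcome

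*Protocol article*

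**What the plan says.** **Claims of blinding.** The Abstract and the Study Design section use the double-blind label; the latter describes "A double-blind, 12-month, parallel-group cluster randomized controlled trial with 1:1 allocation ratio". Randomization and Blinding adds: "The group allocation will remain concealed from both participants and the researcher conducting data analysis". Anticipated Findings presents the evaluation as rigorous, "with blinded outcome assessment and control for potential confounders".

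**What each arm receives.** Under Implementation Protocol, intervention caregivers get the "full version of the iCURE program, including real-time feedback, tailored educational content, and access to the Q&A module". Controls use a simplified version for data collection, and "they will receive no feedback, education, or supplemental materials". Both arms continue to receive routine safety education from preschool teachers and primary care providers. Strategies to Enhance Engagement says that "caregivers in the intervention group will earn lottery entries for completing questionnaires and digital points for viewing educational materials", and that iCURE materials will be "shared through existing WeChat groups by teachers and health care providers in intervention areas".

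**Who reports outcomes.** Data Collection states: "All data will be self-reported, collected via the internet-based iCURE system". The article describes no independent assessor, adjudication or check against medical records.

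**The concern.** Blinded outcome assessment protects a trial when the person deciding whether an outcome occurred does not know, and is not influenced by, the treatment given. Here that person is the caregiver who is the target of the intervention.

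This matters for this primary outcome in particular. Under Outcomes, a child counts as injured if the injury was medically attended and diagnosed, if a non-medical responder such as a family member gave first aid, or if the child missed more than half a day of school. The second criterion depends on the caregiver noticing an injury, deciding to treat it and choosing to report it. Safety education can change each of these steps. Greater awareness would raise reported injuries in the intervention arm and mask a benefit. Reluctance to admit injuries after receiving prevention advice would lower them and imitate a benefit. A reader who takes the blinding claims at face value would give this less weight than it deserves.

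**Working it through.** **1. Claim against description**

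- *Participants do not know their allocation* (Randomization and Blinding). Against this, the list of intervention modules gives all intervention caregivers instant feedback, item-specific reports if the child is classed as high risk, and educational content from once to two or three times a week. Table 1 shows that controls have none of these functions, and no sham content is described. Points for viewing materials can arise only where there are materials to view. The lottery separates the arms less clearly, because Ethical Considerations describes a lottery payment for participants in general.
- *Outcome assessment is blinded* (Anticipated Findings). Against this, Data Collection makes the caregiver the source of all outcome data: the primary outcome, the injury risk level and the supervision score. No other assessor exists to be blinded.
- *The analyst is blinded* (Randomization and Blinding). This can be true. However, Data Analysis enters engagement indicators into the effectiveness model, and Data Collection lists whether, how often and for how long content was viewed. Those viewing measures can be non-zero only in the intervention arm, so they would reveal it. Account subscription exists in both arms and need not reveal it. The article does not say when these variables are merged.
- *Providers.* They customise content and monitor engagement on the web platform, and they share materials in intervention areas. They know their area's arm. Randomization and Blinding does not claim otherwise, but the double-blind label does not make this clear.

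**2. Is a figure in the plan affected?** No. The sample size reproduces. With 15.5% in controls and a 25% reduction, the intervention proportion is 0.155 × 0.75 = 0.11625. A two-sided 5% test with 80% power needs 1225 per arm. Then 2 × 1225 × 1.5 / 0.70 = 5250, which is 1.4% above the stated 5178. The sample size is not in dispute.

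**3. How sensitive is the comparison to differential reporting?** The documents give no rate, so the following is illustrative.

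Let u be the net relative shortfall in the proportion of intervention children reported as injured, with no true effect. The effective number per arm is n = N × 0.70 / 2 / 1.5. For N = 5178 this is 1208; for the enrolled 6701, treated as 1:1, it is 1564. With p1 = p and p2 = p(1 − u),

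P(significant, favouring iCURE) = Φ[(p1 − p2 − 1.96·SE0) / SE1],

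where SE0 = √(2p̄(1 − p̄)/n), p̄ is the mean of p1 and p2, and SE1 = √((p1(1 − p1) + p2(1 − p2))/n).

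Example with u = 10%, p = 0.155: p2 = 0.1395, difference 0.0155, SE0 and SE1 both about 0.0144, so Φ(−0.885) = 18.8%.

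| u | 15.5% incidence, N = 5178 | 9% incidence, N = 6701 |
|---|---|---|
| 0 | 2.5% | 2.5% |
| 5% | 7.7% | 6.5% |
| 10% | 18.8% | 14.5% |
| 15% | 37.1% | 27.6% |
| 20% | 59.5% | 45.4% |
| 25% | 79.5% | 64.7% |

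The 9% column approximates the reported baseline incidences of 8.86% and 9.04%.

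In the opposite direction, take a true 25% reduction and 10% over-reporting in the intervention arm. The apparent risk ratio is 0.75 × 1.10 = 0.825, and power at N = 5178 falls from 80% to 48%. With 5% over-reporting it falls to 65%, and with 20% to 19%.

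**4. What u means.** The outcome counts children, not events. A missed minor injury changes a child's status only if no other injury is reported for that child. A given percentage of unreported events therefore does not translate directly into the same u.

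**The case against.** The article asserts concealment from participants, and nothing in it says that caregivers are told their arm. Allocation is by whole street or town, both arms register for the same account and complete the same baseline surveys, and the consent text is not shown. Control caregivers may well not know that another version exists. Knowing what one receives is also not quite the same as knowing one's allocation. This stands for controls, and it means that their awareness cannot be assumed. It does not rescue the claim of blinded assessment, because intervention caregivers know they are receiving injury-prevention advice and then report the outcome.

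The Discussion also names reporting bias, acknowledges that caregivers may interpret and treat injuries differently, and describes standard definitions and prompts for minor events. That is genuine partial disclosure. However, it treats the problem as general and never as something that could differ between arms, which is the part that biases the comparison.

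A reader might infer that analyst blinding is lost as well. The article does not support this. Only the viewing indicators reveal the arm, and the point at which they are merged is a detail that an analysis plan may settle. It is a risk to manage, not a demonstrated failure.

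**Conclusion.** The concern holds. The double-blind label and the claim of blinded outcome assessment contradict the design in the same article: caregivers report every outcome, and those in the intervention arm visibly receive the intervention. This rests on the article's text and needs no outside figure.

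Neither the direction nor the size of the resulting bias can be determined from the article. The tabulated probabilities show only that modest differential reporting would matter; every value of u is an assumption.

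Two stronger readings are tempting and not supported. One is that no stated protection survives: analyst blinding can still be real, and control caregivers may be unaware of the comparison. The other is that benefit should be concluded only if medically attended injuries point the same way. That would change the decision rule on the strength of a component that is also caregiver-reported, and care-seeking is itself a behaviour that education can change.

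**What to change.** 1. In the Abstract, Study Design, Randomization and Blinding, and Anticipated Findings, replace the double-blind and blinded-assessment wording with: *caregivers and providers not blinded; outcomes caregiver-reported; analyst blinded*. It may be added that control caregivers might not know of the other arm, if the consent text bears this out.
2. In the Discussion, state that reporting may differ by arm, in either direction, as a limitation distinct from general recall bias.
3. Withhold the content-viewing indicators from the analyst until the blinded primary analysis is complete. That analysis is then run without them.
4. Prespecify the treatment effect on injuries meeting the first criterion, medically attended and diagnosed, as a supporting analysis. Describe it as less exposed to differential reporting but not free of it, and do not make it a condition for the conclusion.

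The cost is a change of wording, an order of data release, and one extra analysis of data already covered by the outcome definition. That component will have fewer events and a wider confidence interval. Sample size and treatment are unaffected, and all of this can be settled before the 12-month comparison is unblinded.
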